### Process evaluation

Integral process evaluation informed by existing frameworks [44–46] has three purposes:To examine intervention feasibility, fidelity, reach and acceptability in the feasibility and pilot RCT phasesTo assess provision in control schools and potential contamination in the pilot RCTTo explore context and potential mechanisms of action in the pilot RCT phase, including potential unintended effects, in order to refine the intervention theory of change and design

#### Feasibility assessment phase

The feasibility assessment phase will assess the ‘progression criteria’ to advance to the pilot RCT phase (outlined above). Data will be collected via audio-recording of NCB SEF training for school staff; surveys of school staff trained by NCB SEF; diaries (including time logbooks) of school staff implementing School Health Promotion Councils, curriculum and social marketing meetings; structured observations of two sessions of School Health Promotion Councils, curriculum lessons and social marketing meetings; and individual or group interviews with four NCB SEF staff and four school staff (purposive by role/seniority) and eight year 9 students (purposive by gender and SES).

#### Pilot RCT phase

In addition to assessing the ‘progression criteria’ relating to intervention feasibility and acceptability (outlined above), we will also examine reach via qualitative research as well as questionnaire survey items at follow-up. The information collected on socio-demographic, educational and neighbourhood characteristics in the student surveys will also allow us to examine reach according to these measures and how this varies by institutional setting. We will also assess the fidelity, reach and perceived impacts of staff training activities. Data will be collected via audio-recording of NCB SEF training for school staff; surveys of school staff trained by NCB SEF; diaries (including time logbooks) of school staff implementing School Health Promotion Councils, curriculum and social marketing meetings; and structured observations of randomly selected session per school of School Health Promotion Councils, curriculum lessons and social marketing meetings. Individual or group interviews with two trainers, four staff per intervention school (purposive by seniority/activity involved), and 8 × year 9 students per intervention school, (purposive by involvement, risk status and gender), will also be conducted.

#### Provision in control schools and potential contamination

We will examine sexual health provision in and around control schools in order to describe our comparator. We will examine the potential for contamination across arms to ensure this is not a threat to internal validity in a phase III trial. Data will be collected via student surveys, interviews with two staff per control school (purposive by seniority) and 4 × year-9 students (purposive by gender and SES) per control school.

#### Context and mechanisms of action

In addition to piloting intermediate outcome variables required for mediator analyses in a subsequent phase III RCT, we will use rich, contextual qualitative data and analyse these data in order to explore potential mechanisms of action and thus refine our theory of change. These qualitative analyses will also examine how mechanisms may vary with context, students’ socio-demographic characteristics and/or other factors, in order to refine and optimise the intervention’s theory of change. We will also analyse qualitative data to explore any mechanisms that might give rise to unintended, potentially harmful consequences.

### Economic evaluation

The pilot RCT will examine whether it is feasible to assess cost-effectiveness using a cost-consequence analysis within a phase III trial. Within the pilot, study methods to measure the incremental cost of the intervention in a phase III trial study will be developed and piloted. With the use of a broad public and third sector perspective, resources to be measured will include resources used by NCB SEF, schools and the NHS. Within this, key interventional resources will include NCB SEF and school staff time, training events/workshops and consumables. Measures will include standardised sessional checklists to monitor and document attendance, preparation and delivery time for key training events, School Health Promotion Councils, student-led social marketing meetings and the review of school sexual health services; the completion of surveys and diaries by school staff charged with intervention delivery, assessing time spent on tasks relating to intervention, staff travel and other expenses relating to the intervention charged to a specific project grant code.

The Child Health Utility (CHU) 9D measure [47] will be used to assess student’s health-related quality of life as part of the economic evaluation. The CHU-9 is a validated age-appropriate measure that was explicitly developed using children’s input and has been suggested to be more appropriate and function better than other health utility measures for children and adolescents. Student utility values will be collected (at baseline and at follow-up surveys at 24 and 36 months in a full RCT) using the CHU-9D and by converting the SF-12 questionnaires, respectively. It is anticipated that these measures would be used in a phase III trial to measure short-term impact on health-related quality of life.

### Analyses

#### Feasibility assessment

Our analysis in this phase will determine whether the study should proceed to the pilot RCT phase. Descriptive statistics on fidelity will draw on audio-recordings of training, diaries of providers and structured observations of intervention activities. Analysis of acceptability will draw on interviews with staff and students. Findings will be fed back to NCB SEF staff who will be responsible for refining the intervention ready for implementation in the pilot RCT.

#### Pilot RCT

Our main analyses will determine whether criteria for progression to a phase III trial are met. Descriptive statistics on fidelity will draw on audio-recordings of training, diaries of providers and structured observations of intervention activities. Statistics on acceptability will draw on surveys of students and trained staff and interviews with staff and students. School randomisation and retention, and student follow-up will be described using a CONSORT diagram [48]. We will assess the precision of data linkage in association with ONS researchers.

Additional analyses will address our other research questions. Descriptive summaries of baseline and follow-up data by arm will be tabulated. We will assess the reliability of secondary outcome measures by reporting intra-cluster correlation coefficients (ICC) to examine the consistency of measures from baseline to follow-up (this is different from the use of ICC to measure clustering of variables within schools) and Cronbach’s alpha statistics at baseline and follow-up for scaled outcomes. We will pilot intention-to-treat analyses of outcomes [44] and moderator analyses (how effects vary by SES, gender, ethnicity and baseline risk).

Qualitative data will be subject to thematic content analysis (in vivo/axial codes; constant comparison [49] informed by realist approaches to evaluation [50] and May’s implementation theory [46] to examine potential mechanisms of action and of harm, determine how contextual factors influence implementation and mechanisms, describe relevant activities in and around intervention and control schools and refine our programme theory and theory of change.

Our economic feasibility study will pilot collection of quality of life and assess the feasibility of methods to be used within a full trial, which in line with NICE guidance, would involve a wider cost consequence analysis, comparing intervention costs with the full range of study outcomes.

### Ethical issues

Ethical approval for the study was obtained from the London School of Hygiene and Tropical Medicine Ethics Committee on 21 March 2017 (Ref. 11927).

#### Informed consent

Head teachers as gatekeepers will be asked for informed consent for intervention and random allocation, as is standard practice in cluster randomised trials in schools [42]. As is normal within public health and educational research in secondary schools in the UK (e.g. [34, 35, 37]) informed written opt-in consent will be sought from all research participants, including students, judged competent to provide this (a model information sheet and consent form is provided at Additional file 1). In all cases of data collection including surveys, interviews and focus groups, observations and audio-recordings, except where practically impossible, participants will be given an information sheet several days before data collection. Just before data collection participants will also receive an oral description of the study and have the opportunity to ask questions. Participants will then be advised that participation is voluntary, and they may withdraw at any point. All participants will be advised that they are free to withhold consent, and this matter will not be fed back to teachers or, in the case of staff participants, their managers. Students opting not to participate in surveys will be offered alternative activities in the classroom. Those opting out of other data collection will be free to continue with their normal activities. All participants, including students, will be informed in consent materials of the confidentiality with which the information they provide will be treated as well as the circumstances in which we would need to breach confidentiality (see ‘Safeguarding’ below).

The research will also involve the piloting of the linkage of student survey data to administrative data on births and terminations by the Office for National Statistics. Survey participants will be informed of this process as part of consent procedures and their consent to it sought.

In addition, students’ parents will be contacted by letter 1 week prior to any specific research fieldwork informing them about this and providing them with the option of withdrawing (opting out) their child by contacting the school or the research team. As is normal within public health and educational research involving secondary school students in the UK, we will not seek opt-in consent from student participants’ parents.

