### Randomisation

For the pilot phase, following the baseline survey with students at the end of year 8 (approximately 180 per school), schools will be randomly allocated to intervention/control groups remotely by the Clinical Trials Unit (CTU) at the London School of Hygiene and Tropical Medicine (LSHTM). In the pilot, allocation will be 2:1 favouring the intervention.

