#### Pilot RCT

As already outlined, the pilot RCT will not aim to assess intervention effects, but to assess the feasibility and acceptability of implementing the intervention in state secondary schools in England. Pilot primary outcomes will be meeting criteria for progression to a phase III trial comprising:The intervention is implemented with 70% fidelity in ≥ 3 of four intervention schools.Process evaluation indicates that the intervention is acceptable to 70% of students and staff involved in implementation.Randomisation occurs and ≥ 5 of six schools accept randomisation and continue within the study.Student questionnaire follow-up rates are ≥ 80% in ≥ 5 of SIX schools.Linkage of self-report and routine administrative data on pregnancies is feasible.

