#### Pilot RCT

In the pilot RCT, baseline surveys will be carried out before randomisation as students near the end of year 8 (age 12/13) in June 2018 and will collect data on pre-hypothesised outcome variables, covariates and moderators, drawing on existing survey items as outlined above. Paper questionnaires will be completed confidentially in classrooms supervised by fieldworkers, with teachers remaining at the front of the class to maintain quiet and order, but unable to see student responses. We will survey absent students by leaving questionnaires and stamped addressed envelopes with schools.

We will resurvey students at 12 months (June 2019) as students near the end of year 9 (age 13/14) and will collect self-report data on experiences of the intervention, outcomes and pre-hypothesised potential mediators. Fieldworkers will be blind to allocation. Based on past experience, [37, 42] in the pilot, we expect 95% baseline survey participation and 90% at follow-up. In the pilot, data on terminations and births at 18 months will be obtained in collaboration with the Office for National Statistics (ONS) and the Department of Health (DH) by linking data on female trial participants via the national pupil database and other identifiers to routine ONS data on registration of births and statutory termination notifications, by staff blind to allocation. Linkage of birth and termination data has been previously conducted for observational studies [33] but has not involved linkage to survey data, and hence has not examined participant consent rates, which will be a key focus for our research. Initial discussion with ONS has established that data linkage is feasible despite the limited identifiers attached to termination records and is consistent with DH guidance and data protection law.

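### Students are told that refusal will not be fed back to teachers, yet survey refusers stay in a classroom with the teacher and nothing described hides who is taking part

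*Protocol article*

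**What the plan says.** Under Informed consent, the protocol article says all participants will be advised that "they are free to withhold consent, and this matter will not be fed back to teachers". For surveys the same paragraph adds: "Students opting not to participate in surveys will be offered alternative activities in the classroom". Other data collection is treated differently: "Those opting out of other data collection will be free to continue with their normal activities".

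The Pilot RCT section under Assessment and follow-up describes a confidential paper survey in class, overseen by fieldworkers. On where the teacher is during the session, it has this: "with teachers remaining at the front of the class to maintain quiet and order, but unable to see student responses". It gives the expected response: "we expect 95% baseline survey participation and 90% at follow-up". Among the criteria for progression to phase III (Endpoints of the study, Pilot RCT) is: "Student questionnaire follow-up rates are ≥ 80% in ≥ 5 of SIX schools".

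**The concern.** The assurance is there so that a student can say no without the teacher knowing. The session described puts that student in the same room as a teacher who is there to keep order, doing something other than the survey. No one then has to tell the teacher anything for the refusal to become known. The one stated shield covers what students write, not whether they are taking part.

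Two things are at stake. The first is consent: the students are 12 to 14 years old, the questionnaire asks about sex, pregnancy, sexually transmitted infections and non-volitional sex, and an assurance that is true in wording but weak in effect is a poor basis for voluntary participation. The second is the meaning of the response rate. Follow-up response is a progression criterion, and the section on protection against bias says response rates will be used to refine phase III data collection. If some students take part because declining would be noticed, the recorded rate is higher than it would be with private refusal.

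**Working it through.** **Passages side by side**

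1. Informed consent: researchers will not pass refusals on to teachers.
2. Informed consent, next provision: survey refusers do another activity in the classroom.
3. Assessment and follow-up, Pilot RCT: the teacher is in that classroom, at the front, and cannot see answers.
4. No passage says that participation status is hidden from the teacher.

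Items 2 and 3 give the teacher an opportunity to see what item 1 says will not be reported. Item 1 is not broken, but it does not deliver the privacy that it suggests. The problem is confined to classroom surveys, because students declining other data collection carry on as normal.

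**How many students could be visible**

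Inputs: 6 schools and about 180 students per school (Randomisation); about 1080 students (Analytic sample and proposed sample size); 95% baseline participation (Assessment and follow-up). Class size is not given; I assume 25 to 30.

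- Plan's own figure: 6 × 180 = 1080, which reproduces.
- Non-participants at baseline: 0.05 × 1080 = 54, or 0.05 × 180 = 9 per school.
- Per class: 0.05 × 25 = 1.25; 0.05 × 30 = 1.5.
- Chance that a class has at least one (binomial, probability 0.05): 1 − 0.95^25 = 72%; 1 − 0.95^30 = 79%.
- Chance that a class has two or fewer: 87% (class of 25); 81% (class of 30).

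These are upper bounds for refusers in the room, because the 5% can include absent students and those withdrawn by parents. Under these assumptions a refuser would usually be alone or one of two.

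**What pressure would do to the follow-up rate (illustration only)**

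Let s be the share of respondents who take part only because refusal is visible. The document gives no value for s. With an observed rate of 90%, the rate without that pressure is 0.90 × (1 − s):

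| s | Rate without pressure |
|---|---|
| 2% | 88.2% |
| 5% | 85.5% |
| 10% | 81.0% |
| 15% | 76.5% |

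To bring 90% down to the 80% threshold, s = 1 − 0.80/0.90 = 11%. The criterion is applied school by school, so this overall figure is only a guide.

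**Rare sensitive answers**

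Nothing in the document allows an effect to be computed. It would need the share of unwilling students who give false positive answers to a particular item, and no such figure exists. Blank or evasive forms produce missing or negative answers, so a count of unwilling forms cannot be set against a count of true positives.

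**The case against.** The strongest reply is that there is no literal contradiction. A promise not to feed refusals back binds the researchers, and they can keep it; it does not say that refusal will be invisible. This stands. A reader might infer that the stated protection is false or impossible to honour, but the text does not support that.

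It can also be said that visibility is inferred. The alternative activity is not described, the teacher stays at the front, and a paper task at a desk could look much like the questionnaire. Parents may also withdraw their child, so a non-participant is not necessarily a student who refused. This stands in part: the protocol is compatible with a masked procedure, but it does not describe one, and it does state a shield for answers.

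Seating, pack collection and the wording of the information sheet may lie in the fieldwork instructions or in the supplementary consent form, which are not shown. That is fair, and I make no claim about the sheet's wording. The point rests on two things that the article itself states, not on a missing detail.

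Lastly, if phase III used the same classroom procedure, the rate observed under it would be the relevant one for planning. That limits the consequence for the progression decision. It does not address the quality of consent.

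**Conclusion.** The point holds as an inconsistency between an assurance and the procedure around it. The article tells students that refusal will not be fed back to teachers, then describes a survey session in which the teacher may well see it. The likely direction of any effect on participation is upward. Its size cannot be estimated from the document: about 11% of follow-up respondents would have to be taking part only under pressure to account for the gap between the expected 90% and the 80% criterion, and nothing shows that this is so. The figure of 1.25 to 1.5 non-participants per class assumes classes of 25 to 30 and counts every non-participant as a refuser in the room.

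A reader might go further in two ways, and neither is supported. One is that unwilling forms would swamp true reports of rare behaviours; the document gives no basis for this and says that questionnaires are confidential. The other is that consent to data linkage, which the article calls a key focus, would be biased in the same way; a student who completes the survey but refuses linkage would not stand out by classroom activity.

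This is a modest, cheap improvement to consent procedure and not a demonstrated statistical error.

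**What to change.** For the classroom surveys at baseline and follow-up, give every student the same pack holding the consent page, the questionnaire and a neutral activity sheet. Those who consent complete the questionnaire and the others the activity sheet. All packs go back sealed to the fieldworkers, who alone record consent. State this in the protocol beside the assurance.

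If this is not adopted, limit the assurance to what is delivered: researchers will not report refusals, but the teacher is in the room during the survey.

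The cost is about 1080 activity sheets and envelopes per wave and a line in the fieldwork instructions. The recorded participation rate may fall slightly. On the article's dates (submission in November 2017, pilot baseline survey in June 2018) there was time to make the change before pilot data collection.

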#### Safeguarding

We will develop and maintain standard operating procedures for dealing with safeguarding concerns and reporting serious adverse events. In collaboration with the National Children’s Bureau, we will develop a priori categories of abuse reported through the research that necessitate our breaching confidentiality to ensure individuals are offered care and protection. These criteria will be established so that we balance our ethical duty of promoting participant autonomy by respecting confidentiality and promoting participant wellbeing when we determine that we need to breach confidentiality to address abuse that appears to be serious and ongoing. Where such abuse is reported through a questionnaire, we will contact the safeguarding lead in the school. Where the report occurs directly to research staff, we will first discuss the need for a response with the research participant prior to contacting the school safeguarding lead.

Qualitative research (interviews, focus groups, observations) will not ask staff or students about their experience of sex. However, if participants nonetheless describe any sexual abuse, or otherwise become upset in any way, our researchers will be trained in how to respond. In the case of focus groups, researchers will be trained to ensure that discussions do not move in the direction of personal disclosures of sexual behaviour since this is not the purpose of the groups and it would be very difficult to ensure that all focus group participants did not talk about such disclosures outside the group. Staff will be trained to identify the potential for such disclosures, work to avoid them but then to approach participants immediately after the focus group to offer support and to assess whether any other response is needed, using the same procedures as described above.

Any member of the research/fieldwork team visiting a school will be required to have a full Disclosure and Barring Services (DBS) check. All work will be carried out in accordance with guidelines laid down by the Economic and Social Research Council (ESRC), the Data Protection Act 1998 and the latest Directive on GCP (2005/28/EC).

The trial steering group (which because this is a pilot not a phase III RCT will undertake data monitoring and ethics duties) and the London School of Hygiene and Tropical Medicine ethics committee will be provided with anonymised reports of all disclosures of serious abuse and any other serious adverse events. These will categorised by type, circumstances and the extent of any possible connection with intervention or research activities.

In each school and within NCB a senior member of staff will be identified who is not directly involved with the intervention and whom staff or students may go to if they have complaints about any elements of the research study. This will be communicated to students outside of the research process to increase trust that this is truly independent.

Quantitative and qualitative data will be managed by project staff using secure data management systems and stored anonymously using participant identification numbers. Quantitative data will be managed by London School of Hygiene and Tropical Medicine accredited clinical trials unit (CTU). Where collected, participant identification numbers and corresponding participant names will be held in separate files; these files will be password-protected folders. The names used in qualitative data will be replaced with pseudonyms in interview/focus group transcripts. In reporting the results of the process evaluation, care will be taken to use quotations which do not reveal the identity of respondents.

In line with MRC guidance on personal information in medical research, we will retain all research data for 20 years after the end of the study. This is to allow secondary analyses and further research to take place and to allow any queries or concerns about the conduct of the study to be addressed. In order to maintain the accessibility of the data the files will be refreshed annually and upgraded if required.

